#### **9.5.5.5 Additional therapist training**

As part of the intervention, therapists will receive training in motivational interviewing. Motivational interviewing will equip therapists with the strategies to reinforce engagement, focus on the change required to achieve goals and whether this is clear to the participant or not, evoke motivation for change by e.g., shifting to a greater stage of readiness (“I wish” to “I will”), and plan considering where, when how and with whom.

In particular, the training will focus on strategies for supporting older adults with concerns about falls related to outdoor mobility. We conducted a systematic review (under review at journal) of factors prognostic of concerns about falls following hip fracture. We identified factors amenable to change which therapists can target through motivational interviewing. These factors included fatigue, safe mobility, consequences of not moving, encouragement and feedback, locus of control, self-confidence, and worries about future and past. The training will support therapists to align these factors to the COM-B model of behaviour change and appropriate behaviour change techniques that can be employed through motivational interviewing. Therapists will observe motivational interviewing in practice, practice motivational interviewing themselves, and be provided with access to a recording of the training after the session. They will be offered a revision training session that is therapist-led to discuss any concerns they have in putting motivational interviewing into practice.

#### **9.5.6 Usual care**

The intervention and comparator group will both receive usual care. A survey of UK community rehabilitation for older adults after hip fracture identified two models for those discharged home:

early supported discharge with community rehabilitation for four to six weeks or, discharged home under GP care with referral to community services as needed. Where provided, physiotherapy focused on strengthening exercises (100%), progressive resistance training (91%), weight-bearing exercises (95%), gait training (79%), exercise sheets (91%), encouragement of walking and climbing stairs (98%), and transferring (91%) (mode 30 minutes weekly/fortnightly for 4-6 weeks). Occupational therapy focused on transfer assessment, activities of daily living (e.g., grooming/personal hygiene, dressing, toileting/continence, transferring, and eating), home environment and social support (mode 60 minutes weekly/fortnightly for four to six weeks). Outdoor mobility and behaviour change techniques were not included in routine community rehabilitation.

To enable fidelity assessment (and to monitor for contamination between trial intervention and usual care arms), therapists will complete a study-specific 'usual care' questionnaire after each supervised session of usual care.

### **9.5.7 Outdoor intervention -example of schedule**

#### **• Telephone call 1**

- a. Set outdoor mobility programme goal using motivational interviewing (MI) strategies and behaviour change techniques (BCTs) (e.g. problem solving, action planning, information about health consequences, pros and cons, verbal persuasion about capability). The goal should require outdoor mobility, be meaningful to the patient, and achievable within the scope of the programme.
- b. Determine (logistically) what will be required to complete the outdoor mobility goal e.g. if the goal is to go for coffee with a friend how would they normally get there? Walk to the bus, travel ten stops, short walk to the café, then return. This will allow creation of intermediate goals.
- c. Schedule first home visit.

#### **• Home visit 1**

- a. Show video of older adults discussing their experiences of recovery. Provide piece of paper with link to video to watch again later.
- b. Outline intermediate goals in pursuit of the programme goal.
- c. Practice first intermediate goal while using MI strategies and BCTs (feedback and monitoring, framing/reframing, verbal persuasion about capability).
- d. Set plan for practice between home visits with social support as available (BCT – social support, restructuring the social environment, habit formation).
- e. Provide and describe how to complete home diary.
- f. Schedule next home visit.

#### **• Home visit 2**

- a. Discuss home diary – extent of practice, how felt during and after (MI strategies and BCTs e.g. feedback and monitoring, framing/reframing, verbal persuasion about capability).

- b. Practice intermediate goal while using MI strategies and BCTs (feedback and monitoring, framing/reframing, verbal persuasion about capability).
- c. Progress to next intermediate goal as deemed appropriate.
- d. Set plan for practice between home visits with social support as available (BCT – focus on past success, social support, restructuring the social environment, habit formation).
- e. Schedule next telephone call and home visit.

• **Telephone call 2**

- a. Discuss home diary – extent of practice, how felt during and after (MI strategies and BCTs e.g. feedback and monitoring, framing/reframing, verbal persuasion about capability).
- b. Remind of home visit plan.

• **Home visit 3**

- a. Practice intermediate goal while using MI strategies and BCTs (feedback and monitoring, framing/reframing, verbal persuasion about capability).
- b. Progress to next intermediate goal as deemed appropriate.
- c. Set plan for practice between home visits with social support as available (BCT – focus on past success, social support, restructuring the social environment, habit formation).
- d. Review progress towards programme goal.
- e. Schedule next home visit.

• **Home visit 4**

- a. Discuss home diary – extent of practice, how felt during and after (MI strategies and BCTs e.g. feedback and monitoring, framing/reframing, verbal persuasion about capability).
- b. Practice intermediate goal while using MI strategies and BCTs (feedback and monitoring, framing/reframing, verbal persuasion about capability).
- c. Progress to next intermediate goal as deemed appropriate.
- d. Review progress towards programme goal.
- e. Set plan for practice between home visits with social support as available (BCT – focus on past success, social support, restructuring the social environment, habit formation).
- f. Schedule next telephone call and home visit.

• **Telephone call 3**

- a. Discuss home diary – extent of practice, how felt during and after (MI strategies and BCTs e.g. feedback and monitoring, framing/reframing, verbal persuasion about capability).
- b. Discuss opportunities for community engagement e.g. previous activities or local community activities available through social enterprise groups. This should be guided by the participants interest and activities available in the local area (BCTs – action planning, social support, restructuring the social environment, verbal persuasion about capability).
- c. Remind of home visit plan.

• **Home visit 5**

- a. Discuss home diary – extent of practice, how felt during and after (MI strategies and BCTs e.g. feedback and monitoring, framing/reframing, verbal persuasion about capability).

- b. Practice intermediate goal while using MI strategies and BCTs (feedback and monitoring, framing/reframing, verbal persuasion about capability).
- c. Progress to next intermediate goal as deemed appropriate.
- d. Set plan for practice between home visits with social support as available (BCT – focus on past success, social support, restructuring the social environment, habit formation).
- e. Schedule next telephone call and final home visit.

• **Telephone call 4**

- a. Discuss home diary – extent of practice, how felt during and after (MI strategies and BCTs e.g. feedback and monitoring, framing/reframing, verbal persuasion about capability).
- b. Discuss opportunities for community engagement e.g. previous activities or local community activities available through social enterprise groups. This should be guided by the participants interest and activities available in the local area (BCTs – action planning, social support, restructuring the social environment, verbal persuasion about capability).
- c. Remind of final home visit plan.

• **Home visit 6**

- a. Discuss home diary – extent of practice, how felt during and after (MI strategies and BCTs e.g. feedback and monitoring, framing/reframing, verbal persuasion about capability).
- b. Complete programme goal while using MI strategies and BCTs (feedback and monitoring, verbal persuasion about capability, habit formation).
- c. Set plan for practice going forward with social support as available (BCT – focus on past success, verbal persuasion about capability, social support, restructuring the social environment, habit formation).

## ***9.6 Schedule of Assessments for each visit***

Participants will undergo screening, consent, baseline assessment, assessment at 6- and 12-weeks post-randomisation. We will also complete an assessment at 6 months post-randomisation if the timing of randomisation permits this follow-up within the trial data collection window. All assessments will be completed over the telephone or via MS TEAMS.

Screening (in hospital): Confirmation aged 60 years or more, admitted to hospital from (and planned discharge to) home, with self-reported outdoor mobility in the three-months pre-fracture, surgically treated for hip fracture, able to consent and participate, age, sex, and ethnicity.

Consent (in hospital/at home): Written informed consent to participate (/contact on discharge) will be completed in hospital. For participants who provide consent to contact in hospital, they will be followed up by the community teams to obtain written consent to participate. For those who provide consent/consent-to-contact, fracture type, surgery type, Abbreviated Mental Test and the Clinical Frailty Scale will be collected.

Baseline (at home): Following consent, and prior to randomisation, a member of the research team will collect participant characteristics (see 21.4). They will also collect patient-reported outcome measures which satisfy the core outcome set for hip fracture trials:

- a) death (online death records, screened prior to attempt to contact participant)
- b) health-related quality of life (EuroQoL EQ-5D-5L)
- c) community mobility (University of Alabama Life Space Assessment)
- d) activities of daily living (Nottingham Extended Activities of Daily Living)
- e) falls related self-efficacy (Falls Efficacy Scale-International)
- f) pain (Numeric Rating Scale)
- g) bespoke resource use data collection form (including health and social care, informal care and paid/unpaid work)

6-weeks post randomisation (at home): At 6-weeks post randomisation, a member of the research team will collect the following:

- a) death (online death records, screened prior to attempt to contact participant)
- b) health-related quality of life (EuroQoL EQ-5D-5L)
- c) community mobility (University of Alabama Life Space Assessment)
- d) activities of daily living (Nottingham Extended Activities of Daily Living)
- e) falls related self-efficacy (Falls Efficacy Scale-International)
- f) pain (Numeric Rating Scale)
- g) exercise adherence (Exercise Adherence Rating Scale).
- h) bespoke resource use data collection form (including health and social care, informal care and paid/unpaid work)
- i) hospital readmissions (and reason for readmission)
- j) adverse/serious adverse events (see 11.1)

12-weeks post randomisation (at home): At 12-weeks post randomisation, a member of the research team will collect the following:

- a) death (online death records, screened prior to attempt to contact participant)
- b) health-related quality of life (EuroQoL EQ-5D-5L)
- c) community mobility (University of Alabama Life Space Assessment)
- d) activities of daily living (Nottingham Extended Activities of Daily Living)
- e) falls related self-efficacy (Falls Efficacy Scale-International)
- f) pain (Numeric Rating Scale)
- g) bespoke resource use data collection form (including health and social care, informal care and paid/unpaid work)
- h) exercise adherence (Exercise Adherence Rating Scale).
- i) adverse/serious adverse events (see 11.1)
- j) hospital readmissions (and reason for readmission)
- k) acceptability (brief validated questionnaire)

For intervention participants only, a member of the research team will collect whether the participant engaged family/friends (yes/no) to support them with aspects of the intervention. In addition, the research team will purposively sample participants from different sites with different pre-fracture mobility, living status, and accommodation type for additional telephone/MS TEAMS

semi-structured interviews focused on intervention fidelity (inclusive of barriers and facilitators to implementation). Data collection will continue until no new themes emerge (saturation) or 50% of participants have been interviewed.

6-months post randomisation (at home): At 6-months post randomisation, a member of the research team will collect the following (if the timing of randomisation permits this follow-up within the trial data collection window):

- a) death (online death records, screened prior to attempt to contact participant)
- b) health-related quality of life (EuroQoL EQ-5D-5L)
- c) community mobility (University of Alabama Life Space Assessment)
- d) activities of daily living (Nottingham Extended Activities of Daily Living)
- e) falls related self-efficacy (Falls Efficacy Scale-International)
- f) pain (Numeric Rating Scale)
- g) bespoke resource use data collection form (including health and social care, informal care and paid/unpaid work)
- h) adverse/serious adverse events (see 11.1)
- i) hospital readmissions (and reason for readmission)
- j) death (online death records, screened prior to attempt to contact participant)

Participants who are non-English language speakers will be supported to complete assessments (except patient reported outcome measures) with the use of local interpreting services. Patient-reported outcome measures which have an established translated, validated, and (where applicable) culturally adapted version in the appropriate language will be circulated by post to the participant with a pre-paid envelope for return direct to the research team.

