## **9.9 Withdrawal / dropout of participants**

Participants are free to withdraw from the trial at any point or a participant can be withdrawn by the CI/site PI. No sanctions will follow if the participant decides to leave the research at any time.

Participants who wish to withdraw will have the option of withdrawal from:

- All aspects of the trial but continued use of data collected up to that point.
- All aspects of the intervention but continued use of data collected up to that point and continue with planned completion of questionnaires and interviews as well as collection of information from routine health records for the purpose of primary and some secondary outcomes.
- Any ongoing aspects of the trial that require patient contact or completion of questionnaires, but permission to collection of information from routine health records for the purpose of primary and some secondary outcomes.

Participants can be withdrawn by the CI/site PI following:

- A change in the health status of the participant that the clinical team report justifies withdrawal (including admissions to the inpatient setting).

If withdrawal occurs, the primary reason for withdrawal (as available) will be documented in the participant's case report form (CRF). Participants who withdraw will not be replaced.

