minimising the burden on participants; exercise adherence during intervention delivery for the intervention arm, and participant and therapist acceptability with the use of a brief validated questionnaire at the end of the trial. For those in the intervention arm, we will capture whether participants engaged family/friends (yes/no).

For patients who do not speak English, patient-reported outcome measures which have an established translated, validated, and (where applicable) culturally adapted version in the appropriate language will be circulated by post to the participant with a pre-paid envelope for return. Patient characteristics and additional quantitative outcomes will be collected using local interpreting services.

To assess fidelity for the intervention group, we will audio record intervention sessions between each participant and their supporting physiotherapist/occupational therapist/therapy assistant including discussion of questions/responses recorded in participant diaries (which are to be completed to capture unsupervised outdoor mobility training between visits). The audio recording will enable assessment of the five intervention fidelity domains (design, training, delivery, receipt, and enactment) identified by the National Institute of Health Behaviour Change Consortium. Fidelity assessment will be supplemented by study-specific questionnaires completed by the physiotherapist/occupational therapist/therapy assistant after each supervised session for both intervention and usual care groups.

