Qualitative data on perceived barriers and facilitators to intervention delivery will be captured through purposively sampled (site, pre-fracture mobility, living status, accommodation type, sampled by the research team) remote (telephone/MS TEAMS) semi-structured interviews between a member of the research team and participants (until data saturation is reached). Therapists will contribute their perspectives on barriers and facilitators to intervention delivery in four 60-minute online focus groups via MS TEAMS facilitated by the research team. We will target recruitment of at least 80% of the therapists involved in intervention delivery at each site in each focus group. We will also extend invitations for interviews between a member of the research team and people at higher organisational levels (e.g., local allied health professional community team leaders and service managers) for their perspectives on potential barriers and facilitators.

Data collection forms (including topic guides) are detailed in additional files.

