### **12.2.3 Qualitative data**

For intervention group participants, all supervised treatment sessions will be audio-recorded to enable a direct assessment of treatment fidelity (primary objective). These audio-recordings will be uploaded by the therapist to a secure KCL SharePoint server accessible only to the research team, labeled with the participant identification number after which the recording will be deleted from the audio recording device.

For a sample of participants, the research team will audio-record semi-structured interviews completed at the end of their time in the trial. The research team will also audio-record semi-structured interviews with local allied health professional community team leaders and service

managers completed by MS TEAMS and focus groups with therapists via MS TEAMS. These audio-recordings will be uploaded by the research team to a secure KCL SharePoint server accessible only to the research team, pseudo-anonymised with the participant identification number/file identification number (for leaders, managers and focus groups) after which the recording will be deleted from the audio recording device. These recordings will be transcribed verbatim and anonymised after which the audio-files will be permanently deleted.

Following publication of the primary paper, anonymised transcriptions of interviews will be stored on the King's Open Research Data System indefinitely (<https://www.kcl.ac.uk/researchsupport/managing/preserve>), with proof of ethical approval as a condition of access.

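### Participants who leave contact before 12 weeks give no acceptability score, and the interview frame does nothing to ensure that early stoppers of the intervention are heard

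*Protocol*

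**What the plan says.** **Acceptability score.** Section 9.6 lists the participant questionnaire at 12 weeks and at no other visit, and Table 1 (21.4) marks the same single time point. Section 12.1 describes "participant and therapist acceptability with the use of a brief validated questionnaire at the end of the trial". In Figure 3 (21.3) the participant row is GO at a median of 28 or more, AMEND at 24 to 27 and STOP below 24, on a scale from 8 to 40. Figure 3 gives no rule for a participant without a score.

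**Withdrawal.** Section 9.9 offers three options.
- Option 1 is withdrawal from "All aspects of the trial but continued use of data collected up to that point".
- Option 2 is withdrawal from "All aspects of the intervention but continued use of data collected up to that point and continue with planned completion of questionnaires and interviews".
- Option 3 ends contact and questionnaires but leaves access to routine records.

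The main reason for leaving is recorded where it can be obtained.

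**Interviews.** Section 9.6 plans to "purposively sample participants from different sites with different pre-fracture mobility, living status, and accommodation type", and 12.1 repeats the same four factors. The stopping rule in 9.6 is "Data collection will continue until no new themes emerge (saturation) or 50% of participants have been interviewed". Section 12.2.3 describes "semi-structured interviews completed at the end of their time in the trial", and Table 1 places patient interviews at 12 weeks.

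**The concern.** Acceptability and barriers to delivery are the first two secondary objectives (6.3), and participant acceptability has its own progression row. A person who finds the programme unacceptable is a plausible candidate to leave it. If that person also leaves contact, the 12-week questionnaire never reaches them, and the median is taken over people who tolerated the programme well enough to stay. Missing scores would then be related to the quantity being measured.

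The interviews could make up for this, because they are meant to explain barriers. But the frame varies people by where they were recruited, how they moved before the fracture, and how and where they live. It does not vary them by what happened to them in the intervention. A sample can be well spread on all four factors and consist entirely of completers. A definitive trial would then be planned without the first-hand reasons for stopping that it most needs.

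**Working it through.** **1. Who is left without a score.** Setting 9.9 against 9.6:

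| Participant | 12-week score due? | Can be interviewed? |
|---|---|---|
| Withdraws from everything before 12 weeks (option 1) | No | No |
| Stops the intervention only (option 2) | Yes | Yes, but not sampled for |
| Refuses contact and questionnaires (option 3) | No | No |
| Lost before 12 weeks | No | No |

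**2. How many.** Section 13.1 plans 30 per arm and 80% retention at 12 weeks. Its own figures reproduce. The exact 95% interval for 48 of 60 is 67.7% to 89.2%, a half-width of 10.8 points, which rounds to the stated ±11%. Per arm, 30 × 0.80 = 24 followed up, so 30 − 24 = 6 intervention participants may have no score. I take the Figure 3 row to refer to the intervention arm.

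**3. Largest shift of the median.** Suppose all 6 would have scored below every respondent.
- The median of 30 lies at rank (30 + 1)/2 = 15.5.
- Among the 24 respondents in ascending order, this is rank 15.5 − 6 = 9.5.
- As a quantile it is (9.5 − 0.5)/24 = 0.375, the 37.5th percentile of the observed scores.
- Under a normal approximation this lies 0.32 SD below the observed median.

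The documents give no SD for the score. For an assumed SD of 3 the fall is 0.96 points, and for an assumed SD of 6 it is 1.91 points.

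**4. A milder case.** Suppose 3 of the 6 would have scored at the bottom, and the other 3 are left out as if they would have resembled the respondents. The median of 27 lies at rank 14, which is rank 14 − 3 = 11 among the 24. The quantile is (11 − 0.5)/24 = 0.4375, or 0.16 SD lower: 0.5 to 0.9 points for the same range of SD.

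**5. What this does to the row.** With a fall of at most 1.91 points, an observed median of 28 or 29 could move from GO to AMEND. An observed 30 becomes at lowest 30 − 1.91 = 28.09 and stays GO.

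**6. Check by counting, without an SD.** If 13 or more of the 24 respondents score at least 28, the observed median is GO. If all 6 others are below 28:
- 13 or 14 of 30 at or above 28 puts the median of 30 below 28.
- 15 of 30 leaves it undecided, because the median then averages one value on each side of the line.
- 16 or more keeps it at GO.

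If instead 3 of the 6 would have scored 28 or more, then 13 + 3 = 16 and GO stands in every case where at least 13 respondents reached 28.

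**7. Interview cap.** If the 50% refers to the 30 intervention participants, at most 15 are interviewed. None of the four factors reserves a place for someone who stopped early.

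**The case against.** The strongest reply is that people who stop the intervention are not lost. Option 2 in 9.9 keeps them in questionnaires and interviews. This stands, and it confines the scoring gap to options 1 and 3 and to losses before 12 weeks.

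Barriers also have other planned sources: therapist focus groups, manager interviews, session recordings, therapist questionnaires after each session, and recorded reasons for withdrawal. This stands too, although none of these is a planned interview with the person who left.

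The 20% loss is assumed equal in both arms, and the control arm has no intervention to reject. Section 9.9 also allows withdrawal for a change in health, and some losses will be deaths. The case with all 6 at the bottom is therefore an upper bound.

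Figure 3 has a separate row for 12-week EQ-5D completeness, and 13.2 plans completion rates. Heavy loss would show there. The planned loss would not: 48/60 = 80%, which still meets GO if every retained participant completes the EQ-5D.

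Reporting of missing scores may be left to the SAP, which is not shown. That is fair for the sensitivity median. It does not help with scores that were never collected or interviewees who were never sampled.

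Finally, a questionnaire triggered by stopping could reveal allocation. Section 9.4 blinds the assessors of patient-reported outcomes, Table 1 has the research team collect acceptability, and unblinding is itself counted as an objective. This stands and shapes the fix.

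**Conclusion.** The point holds in a limited form. Full withdrawers, those who refuse further contact, and those lost before 12 weeks contribute nothing to the acceptability median. Early stoppers who stay in follow-up are eligible for interview but are not deliberately sampled.

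The effect on the progression row is at most about 0.32 SD, or 1 to 2 points. This rests on three assumptions that the documents do not supply: an SD of 3 to 6, approximate normality, and all 6 losses scoring at the bottom. It is smaller if losses are for death or ill health, and it matters only when the observed median is at or just above 28.

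A reader might infer two stronger things. One is that everyone who stops because the intervention is unacceptable is missing from both the score and the barriers analysis; option 2 and the other barrier sources contradict that. The other is that the row is likely to return a false GO. The documents give neither the distribution of scores nor the reasons for leaving, so no probability can be attached to that, and an upward bias is plausible rather than shown.

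**What to change.** 1. Add intervention completion status (completed, stopped early, declined) to the purposive sampling factors in 9.6 and 12.1.
2. Report the Figure 3 participant-acceptability row with the number of intervention participants without a score, and with a sensitivity median that counts them below the GO line.
3. In 9.6 and 9.9, offer the eight-item questionnaire at the point of stopping or withdrawal to those willing. It should be optional and administered by someone other than the blinded outcome assessor.

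Section 13.2 summarises acceptability at each follow-up although it is scheduled only at 12 weeks. The two should be reconciled in the same edit.

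The cost is one more sampling characteristic, one more reported line and a short optional form that needs a person outside the blinded team. Some leavers will decline and those lost to follow-up cannot be asked, so the gap narrows but does not close. The acceptability result may also be less favourable. No extra participants are needed.
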